## Abstract

**Introduction:**

COVID-19 may lead to long-term endothelial consequences including hypertension, stroke and myocardial infarction. A pilot study ‘COVID-19 blood pressure endothelium interaction study’, which found that patients with normal blood pressure (BP) at the time of hospital admission with COVID-19 showed an 8.6 mm Hg higher BP ≥12 weeks after recovery, compared with a group without COVID-19. The ‘LOnger-term effects of SARS-CoV-2 INfection on blood Vessels And blood pRessure’(LOCHINVAR) study is designed to provide definitive evidence of the long-term impact of COVID-19 on BP.

**Methods and analysis:**

The LOCHINVAR study is an observational clinical phenotyping study comparing longitudinal BP change between individuals with and without COVID-19 infection. 150 participants (30–60 years) with no history of hypertension and not on BP lowering medications will be recruited to the study to attend three visits (baseline, 12 months, 18 months). Cases will be patients who were admitted to the Queen Elizabeth University Hospital (QEUH), Glasgow, UK, with suspected/confirmed COVID-19 until 31 December 2021 and who were alive at discharge. Controls will be those who have never had confirmed COVID-19 infection. All participants will undergo clinical and vascular phenotyping studies which will include 24-hour ambulatory BP monitoring systolic BP (ABPM SBP), brachial flow-mediated dilatation urine and blood samples to assess the renin-angiotensin system, vascular inflammation and immune status. The primary outcome is the change in systolic 24-hour ABPM (ABPM SBP) between the cases and controls. Sample size was calculated to detect a mean difference of 5 mm Hg ABPM SBP at 80% power.

**Ethics and dissemination:**

The protocol of this study has been approved by the West of Scotland Research Ethics Committee 5 (21/WS/0075), Scotland, UK. Written informed consent will be provided by all study participants. Study findings will be submitted to international peer-reviewed hypertension journals and will be presented at international scientific meetings.

**Trial registration number:**

NCT05087290.

What is already known on this topicCOVID-19 may lead to long term endothelium dysfunction however the evidence of this is limitedWhat this study addsThe LOCHINVAR study is an 18-month follow-up study of non-hypertensive adults who have recovered from COVID-19 and those with no history of COVID-19. It will determine if there is a sustained increase in blood pressure beyond 12 months post-COVID-19 and whether this is related to endothelial dysfunction or perturbations of the renin-angiotensin system.How this study might affect research, practice and/or policyThis study will help generate crucial evidence on the long-term impact of COVID-19 on blood pressure and will facilitate the prioritisation of targetable molecular pathways that can progress into potential therapies and clinical trials.

## Introduction

COVID-19 is an acute respiratory disease caused by the SARS-CoV-2 virus and declared a pandemic on 11 March 2020 by the WHO.^1^ SARS-CoV-2 enters target host cells through the interaction of the spike glycoprotein (S) with ACE2 on the target cell membrane serving as the SARS-CoV-2 receptor.^2^ ACE2 is a component of the renin-angiotensin system (RAS) and catalyses the conversion of Ang II to Ang-(1-7), a vasoprotective Ang II-derived peptide and plays an important role in blood pressure (BP) regulation.^3^ ACE2 is found in type 2 pneumocytes, macrophages, perivascular pericytes, cardiomyocytes and possibly endothelial cells, indicating the possible routes of infection by SARS-CoV-2,^2^ and potential consequences beyond the lungs especially the cardiovascular system^3^ leading to myocardial and endothelial dysfunction.^3^ Cardiovascular consequences are likely to be induced by severe systemic inflammatory cytokine storm, in patients with SARS-CoV2 requiring hospitalisation.^3^ Cardiac dysrhythmia, cardiac injury, myocarditis, heart failure, pulmonary embolism and disseminated intravascular coagulation are reported complications of COVID-19 lending credence to the extrapulmonary impact of COVID-19.^3^ Furthermore, epidemiological data suggest those at high cardiovascular risk (hypertension, obesity, diabetes) or those with prevalent cardiovascular disease are at higher risk of severe COVID-19.^4^ It is unclear if antihypertensive drugs that block the RAS (ACE inhibitors or angiotensin receptor blockers) alter prognosis in those with COVID-19 infection.^3^

Prior studies on the relationship between COVID-19 and the cardiovascular system are limited by case selection and retrospective data collection. A prospective pilot study ‘COVID-19 BP endothelium interaction study’ (ClinicalTrials.gov NCT04409847, funded by the Chief Scientific Office)^5^ compared 12-week postdischarge ambulatory BP measurements in non-hypertensive patients discharged from hospital after an admission with COVID-19 or a non-COVID diagnosis. This study showed that non-hypertensive COVID-19 patients had an 8.6 mm Hg higher 24-hour systolic BP (SBP) at 12 weeks postdischarge compared with those that did not have COVID-19 infection. A definitive prospective study with longer follow-up is required to confirm if BP is higher in post-COVID-19 patients and whether the higher BP is sustained over a longer period. The LOnger-term effects of SARS-CoV-2 INfection on blood Vessels And blood pRessure (LOCHINVAR) study is designed to answer this question along with pathophysiological studies through deep vascular phenotyping and biomarker studies of endothelial function and vascular injury. The LOCHINVAR study will help generate crucial evidence on the long-term impact of COVID-19 on BP and with information from our mechanistic studies which will facilitate the prioritisation of targetable molecular pathways that can rapidly progress into potential therapies and clinical trials.^6^

## Methods and analysis

### Study design

The LOCHINVAR study is a single-centre clinical study designed to determine the long-term impact of COVID-19 on BP. This study is a follow-up of the pilot COVID-19 blood pressure endothelium interaction study (OBELIX) study (ClinicalTrials.gov NCT04409847) which showed increased ambulatory BP monitoring (ABPM) SBP in COVID-19 patients postrecovery compared with contemporaneous non-COVID controls.

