### Study participants, screening and recruitment

The study design, study visit schedule and inclusion/exclusion criteria is shown in figure 1. One hundred and fifty participants aged between 30 and 60 years in the National Health Service (NHS) Greater Glasgow and Clyde health board catchment area, will be invited to take part in the study to attend three study visits (baseline, 12 months and 18 months). Patients, who do not have a history of high BP or hypertension treatment, admitted through the QEUH immediate assessment unit and acute receiving units with suspected/confirmed COVID-19 between 1 September 2020 and 31 December 2021 will be invited after at least 12 weeks postdischarge. The clinical criteria for clinically suspected COVID-19 include either fever, new-onset cough and/or anosmia/dysgeusia and/or ≥2 of the following presenting features: fatigue/generalised weakness, headache, myalgia, sore throat/coryzal symptoms, breathlessness, anorexia/nausea/vomiting, diarrhoea, contact with known COVID-19 positive case. Patients who are SARS-CoV-2 RT-PCR positive and/or have diagnostic chest X-ray or CT features of COVID-19 will be classified as cases.

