**Figure 1 F1:**
[figure not shown]
Study design, inclusion and exclusion criteria and study procedures. ABPM, ambulatory blood pressure monitoring; AF, atrial fibrillation; BMI, body mass index; BP, blood pressure; eGFR, estimated glomerular filtration rate; IAU, Immediate Admissions Unit. NSAID, non-steroidal anti-inflammatory drugs; OBELIX, COVID-19 blood pressure endothelium interaction study; QEUH, Queen Elizabeth University Hospital Glasgow; SBP, systolic blood pressure.

Control participants will be recruited from hospital admission records or through advertisement. Control patients recruited from hospital admission records will have an admission with COVID-19 like symptoms but are SARS-CoV-2 RT-PCR negative and have chest X-ray or CT (if performed during the relevant admission) that show low probability of COVID-19 and are SARS-CoV-2 IgG antibody negative at enrolment.

Controls recruited through advertising should have had no history of SARS-CoV-2 infection or have had a negative RT-PCR test previously and should have a negative SARS-CoV-2 IgG antibody test at enrolment. Controls will be matched for age, sex and diabetes status with cases by review of demographics of recruited cases and controls at 3 monthly intervals.

OBELIX participants have consented to be recontacted and will be invited to take part in the 12-month and 18-month follow-up visits in the LOCHINVAR study.

Screening for eligibility of all potential participants will be carried out by a member of the study team through review the electronic health record and electronic prescribing records or questionnaire responses. All participants identified as potentially eligible based on the inclusion criteria will be given a participant information sheet for the study containing contact details for the study team and given sufficient time to consider taking part. If the participant is interested, they will contact a member of the study team to discuss further and if they confirm interest in participating in the study, they will provide written, informed consent. Participants may withdraw from the study at any time.

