### Statistical analysis

The primary analysis (primary outcome 24-hour ABPM SBP at 12 months) will use linear regression to compare 24-hour ABPM SBP between SARS-CoV-2 positive and SARS-CoV-2 negative subjects with adjustment for covariates including age, sex and BMI. The adjusted mean difference, with a 95% CI and associated p value, will be reported.

Secondary analyses will extend this regression model to examine the impact of baseline patient characteristics, and to investigate the possibility of interactions with COVID-19 clinical status. For longitudinal analysis we shall use linear mixed models as appropriate to compare changes in the mean 24-hour ABPM SBP between SARS-CoV-2 positive and SARS-CoV-2 negative subjects with adjustment for baseline 24-hour ABPM SBP and baseline covariates.

All statistical analyses will be performed using R Software V.4.0.2 or later.

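### The 12-month comparison uses no pre-infection BP, so a BP difference that existed before COVID-19 cannot be told apart from an effect of it, and the causal aim is stated too strongly

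*Protocol article*

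**What the plan says.** The aim is causal: Study design describes a "single-centre clinical study designed to determine the long-term impact of COVID-19 on BP", and the Abstract promises definitive evidence of that impact.

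- **Cases** are patients admitted to one hospital with COVID-19 who "will be invited after at least 12 weeks postdischarge". The restriction on prior BP, as given in the text, is to people "who do not have a history of high BP or hypertension treatment".
- **Controls:** "Control participants will be recruited from hospital admission records or through advertisement". The hospital-recruited ones had COVID-like symptoms but tested negative. Matching is on age, sex and diabetes.
- **Eligibility** is checked "through review the electronic health record and electronic prescribing records or questionnaire responses".
- **Primary outcome** (Primary outcome section): the mean 24-hour systolic BP at 12 months in each group.
- **Primary model** (Statistical analysis): linear regression "with adjustment for covariates including age, sex and BMI". Baseline 24-hour systolic BP enters only the longitudinal mixed model.

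The Introduction states that "those at high cardiovascular risk (hypertension, obesity, diabetes) or those with prevalent cardiovascular disease are at higher risk of severe COVID-19".

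**The concern.** The case group is defined by being ill enough with COVID-19 to be admitted. The article itself names hypertension and high cardiovascular risk as drivers of severe disease, so a precursor of the outcome may influence entry to the case group. If cases had higher BP than controls before infection, a comparison of levels at 12 months would show that difference whether or not COVID-19 raised anyone's BP.

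Longer follow-up does not separate the two explanations. A stable difference at 12 and 18 months is what a lasting COVID-19 effect would produce, and it is also what selection on prior BP would produce. At stake is whether a positive result can be reported as an effect of infection, which is how the objective is worded.

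**Working it through.** **Step 1. Is there a pre-infection BP anywhere in the comparison?**

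| Element | Handles prior BP? |
|---|---|
| Exclusion of known hypertension or treatment | In part: removes recognised hypertension, not undiagnosed or high-normal BP |
| Matching on age, sex, diabetes | Indirectly |
| Adjustment for age, sex, BMI (an open list) | Indirectly; no prior BP is named |
| Hospital-recruited controls | In part: they share selection into admission, but their share of the controls is not stated |
| Baseline BP in the mixed model | No: for newly recruited cases it is measured at least 12 weeks after discharge |

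The last row matters. Adjusting for a post-infection baseline removes a prior gap and any early COVID-19 rise together, so it does not isolate either.

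**Step 2. Reproduce the plan's own figure.** Inputs from Sample size calculation: difference 5 mm Hg, SD 10, power 80%. The printed alpha is 0.05%; two-sided 5% is used here because it reproduces the stated number.

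n per group = 2 × (1.960 + 0.842)² × (10/5)² = 62.8, so 63 by the normal approximation and 64 by the t-test. This agrees with the stated 64. Allowing for 15% loss, 128/0.85 = 150.6, against the stated 150.

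**Step 3. How large could a prior gap be?** Assumption: prior 24-hour systolic BP is normal with SD 10 (the plan's SD), and the risk of admission with COVID-19 is multiplied by r for each 10 mm Hg, among people otherwise alike on the matching and adjustment factors. Weighting a normal density by exp(x · ln r / 10) moves its mean by SD² × ln(r)/10 = 10 ln(r).

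| r (assumed) | Prior gap, mm Hg |
|---|---|
| 1.05 | 0.49 |
| 1.1 | 0.95 |
| 1.2 | 1.82 |
| 1.3 | 2.62 |

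No value of r is given in the article. For hospital-recruited controls, only the excess of this gradient over that for other admissions would count.

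**Step 4. Shrinkage from excluding hypertension.** Illustration with an assumed control mean of 120, SD 10, and both groups cut off at 130, 135 or 140 mm Hg:

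| Gap before exclusion | Cut 130 | Cut 135 | Cut 140 |
|---|---|---|---|
| 2 | 1.20 | 1.49 | 1.73 |
| 3 | 1.76 | 2.19 | 2.57 |

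So even a strict cut-off leaves roughly 60% to 86% of the gap.

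**Step 5. What would a leftover gap do to the test?** With 64 per group, SE = 10 × √(2/64) = 1.77 mm Hg. With no true COVID-19 effect and a leftover gap d, the chance of a two-sided p < 0.05 is Φ(d/SE − 1.96) + Φ(−d/SE − 1.96):

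| d, mm Hg | Chance of significance |
|---|---|
| 0 | 5% |
| 1 | 9% |
| 2 | 20% |
| 2.5 | 29% |
| 3 | 40% |

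The sample size is correct for its purpose, but it gives no protection against this bias.

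**The case against.** The strongest reply is that the design already addresses each risk factor the Introduction names. Hypertension is excluded, diabetes is matched and obesity is handled through BMI. Some controls were admitted with similar symptoms. The covariate list is open, the full eligibility criteria are in Figure 1 (not shown), and the study calls itself observational. Much of this stands and limits the point.

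Three stronger readings are tempting and are not supported:

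- **That cases are enriched for higher prior BP.** The Introduction speaks of hypertension as a category. It does not say that risk rises with BP within the non-hypertensive range, so enrichment is possible but not established.
- **That the model adjusts for age, sex and BMI and nothing else.** The wording says that the covariates include these. What can be said is that no pre-infection BP is named.
- **That high-normal BP is certainly admitted.** Figure 1 may contain a BP limit. If so, it would narrow a gap but would not put pre-infection BP into the analysis.

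A reader might also point to the Abstract, which words the primary outcome as a change. Change from a post-infection baseline would cancel a constant prior gap, but it would equally cancel any rise that occurred before that baseline.

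Nor is this only a detail left to an analysis plan. The causal objective is stated here, and no analysis plan can adjust for a value that was never collected.

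**Conclusion.** The point holds as a limit on what the study can conclude. A 12-month difference in level between admitted COVID-19 patients and these controls shows an association. As described, the analysis cannot separate BP that was already higher from BP that rose after infection.

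The size cannot be derived from the article. Under the assumed r of 1.05 to 1.3 and SD 10, the prior gap is about 0.5 to 2.6 mm Hg before shrinkage, that is 10% to 52% of the 5 mm Hg target. At the low end the effect on the result is small: a 1 mm Hg gap takes the false-positive rate from 5% to about 9%. At the upper end it is material: a leftover 2 mm Hg gives about 20%. Nothing in the article says which end is nearer the truth. It would be wrong to infer that the pilot's 8.6 mm Hg difference, or a future positive result, is explained by selection; even the top of the assumed range falls well short of 8.6. The point merits a change to data collection and wording. It does not invalidate the design.

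**What to change.** 1. Where the health record is reviewed for eligibility, extract the most recent BP recorded before the index admission (before enrolment for advertised controls), with its date and setting.
2. Prespecify a supporting analysis: the 12-month difference adjusted for that BP as well as the primary covariates, in participants who have one. Report the estimate, its 95% CI and the number available per group. Do not use it as a pass/fail gate; the subset will be selected and the readings noisy.
3. Report the primary difference separately against hospital-recruited controls, who share selection into admission.
4. Word the primary conclusion as an association with hospitalised COVID-19, and temper the Abstract's promise of definitive evidence to match.

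**Cost.** One extra data item and two supporting analyses. The primary model and sample size are unchanged, and the rewording needs no data. Prior BPs will be incomplete and non-standardised, especially where screening was by questionnaire and no record was opened; a routine clinic reading also adjusts only in part for 24-hour BP. The hospital-control comparison will be less precise. If half of the 64 controls were hospital-recruited (an assumption; the split is not stated), SE = 10 × √(1/64 + 1/32) = 2.17 mm Hg, so the 95% CI would extend about ±4.2 mm Hg, against ±3.5 with all controls.

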### Study participants, screening and recruitment

The study design, study visit schedule and inclusion/exclusion criteria is shown in figure 1. One hundred and fifty participants aged between 30 and 60 years in the National Health Service (NHS) Greater Glasgow and Clyde health board catchment area, will be invited to take part in the study to attend three study visits (baseline, 12 months and 18 months). Patients, who do not have a history of high BP or hypertension treatment, admitted through the QEUH immediate assessment unit and acute receiving units with suspected/confirmed COVID-19 between 1 September 2020 and 31 December 2021 will be invited after at least 12 weeks postdischarge. The clinical criteria for clinically suspected COVID-19 include either fever, new-onset cough and/or anosmia/dysgeusia and/or ≥2 of the following presenting features: fatigue/generalised weakness, headache, myalgia, sore throat/coryzal symptoms, breathlessness, anorexia/nausea/vomiting, diarrhoea, contact with known COVID-19 positive case. Patients who are SARS-CoV-2 RT-PCR positive and/or have diagnostic chest X-ray or CT features of COVID-19 will be classified as cases.

**Figure 1 F1:**
[figure not shown]
Study design, inclusion and exclusion criteria and study procedures. ABPM, ambulatory blood pressure monitoring; AF, atrial fibrillation; BMI, body mass index; BP, blood pressure; eGFR, estimated glomerular filtration rate; IAU, Immediate Admissions Unit. NSAID, non-steroidal anti-inflammatory drugs; OBELIX, COVID-19 blood pressure endothelium interaction study; QEUH, Queen Elizabeth University Hospital Glasgow; SBP, systolic blood pressure.

Control participants will be recruited from hospital admission records or through advertisement. Control patients recruited from hospital admission records will have an admission with COVID-19 like symptoms but are SARS-CoV-2 RT-PCR negative and have chest X-ray or CT (if performed during the relevant admission) that show low probability of COVID-19 and are SARS-CoV-2 IgG antibody negative at enrolment.

Controls recruited through advertising should have had no history of SARS-CoV-2 infection or have had a negative RT-PCR test previously and should have a negative SARS-CoV-2 IgG antibody test at enrolment. Controls will be matched for age, sex and diabetes status with cases by review of demographics of recruited cases and controls at 3 monthly intervals.

OBELIX participants have consented to be recontacted and will be invited to take part in the 12-month and 18-month follow-up visits in the LOCHINVAR study.

Screening for eligibility of all potential participants will be carried out by a member of the study team through review the electronic health record and electronic prescribing records or questionnaire responses. All participants identified as potentially eligible based on the inclusion criteria will be given a participant information sheet for the study containing contact details for the study team and given sufficient time to consider taking part. If the participant is interested, they will contact a member of the study team to discuss further and if they confirm interest in participating in the study, they will provide written, informed consent. Participants may withdraw from the study at any time.

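### The primary model does not name diabetes, a matching factor, and no comparison with hospital controls is stated although all cases were admitted and some controls need not have been

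*Protocol article*

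**What the plan says.** All of the following is in the protocol article.

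- **Cases** (Abstract, Methods and analysis): "Cases will be patients who were admitted to the Queen Elizabeth University Hospital (QEUH), Glasgow, UK, with suspected/confirmed COVID-19".
- **Controls** (Study participants, screening and recruitment): "Control participants will be recruited from hospital admission records or through advertisement". The two routes differ in what they require. For the first, "Control patients recruited from hospital admission records will have an admission with COVID-19 like symptoms but are SARS-CoV-2 RT-PCR negative". For the second, "Controls recruited through advertising should have had no history of SARS-CoV-2 infection or have had a negative RT-PCR test previously", together with a negative antibody test at enrolment; no admission is needed. No split or cap between the routes is given.
- **Matching** (same section): "Controls will be matched for age, sex and diabetes status with cases by review of demographics of recruited cases and controls", with the review done every 3 months. This is group-level (frequency) matching on three factors.
- **Primary model** (Statistical analysis): linear regression of 12-month 24-hour systolic pressure on SARS-CoV-2 status, "with adjustment for covariates including age, sex and BMI". Diabetes and control source are not named. Secondary analyses extend this model to baseline characteristics that are not listed, and a longitudinal mixed model adjusts for baseline ambulatory pressure.
- **Pilot** (Introduction): COVID-19 and non-COVID patients were compared after discharge, so both groups had been admitted.

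**The concern.** Two separate gaps affect the same coefficient, and they differ in weight.

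The smaller one is a mismatch between design and model. Three factors are used to balance the groups and only two of them are named for adjustment. Frequency matching by periodic review is approximate, and the Sample size calculation expects about 15% missing data and ABPM errors. Balance at recruitment therefore need not carry over to the analysed set.

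The larger one is the choice of comparator. Cases are defined by an admission; advertised controls are not. If people who have been admitted differ in blood pressure from people who answer an advertisement, for reasons other than COVID-19, part of that difference enters the coefficient that will be read as the COVID-19 effect. The pilot avoided this by comparing two admitted groups. The present design relaxes that feature, while the Abstract aims at definitive evidence on the long-term impact of COVID-19 on blood pressure.

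**Working it through.** **Inputs from the article (Sample size calculation):** difference 5 mm Hg, SD 10 mm Hg, 64 per group, 80% power, 150 recruited for 128 completers, about 15% loss.

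**Inputs assumed, because the article gives none:** advertised share of controls 30% to 50%; systolic pressure in advertised controls 2 to 4 mm Hg below that in hospital controls; residual diabetes imbalance 5 to 10 percentage points; diabetes effect on systolic pressure 5 to 8 mm Hg.

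**Step 1. Reproduce the stated sample size.** A two-sample t-test with standardised difference 5/10 = 0.5 and two-sided alpha 0.05 needs 63.8, so 64 per group, with power 80.1%. Inflation gives 128/0.85 = 150.6, or 151 against the stated 150. The figures agree, reading the printed alpha as 0.05.

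**Step 2. Bias from control source.** With no term separating the two kinds of control, bias = advertised share × gap.

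- Low end: 0.30 × 2 = 0.6 mm Hg, which is 12% of 5 mm Hg.
- High end: 0.50 × 4 = 2.0 mm Hg, which is 40% of 5 mm Hg.
- With a zero advertised share or a zero gap the bias is zero. If advertised controls had the higher pressure, the sign would reverse.

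**Step 3. Bias from diabetes.** Bias = imbalance × effect.

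- Low end: 0.05 × 5 = 0.25 mm Hg.
- High end: 0.10 × 8 = 0.8 mm Hg.

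**Step 4. What such a bias does to the test.** The standard error of the primary contrast is 10 × √(2/64) = 1.77 mm Hg. With no true COVID-19 effect and bias b, the two-sided rejection rate is P(Z > 1.96 − b/1.77) + P(Z < −1.96 − b/1.77).

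| Bias (mm Hg) | Possible source under the assumptions | Type I error (nominal 5%) |
|---|---|---|
| 0.25 | diabetes, low end | 5.2% |
| 0.6 | control source, low end | 6.3% |
| 0.8 | diabetes, high end | 7.4% |
| 1.0 | control source, 0.50 × 2 | 8.7% |
| 2.0 | control source, high end | 20% |

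**Step 5. Cost of adding diabetes.** Take prevalences of 15% and 5% as an illustration. The squared correlation between group and diabetes is 0.05²/(0.10 × 0.90) = 0.028, so the variance inflation is 1/(1 − 0.028) = 1.03. Power stays at about 80%.

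**Step 6. Precision of cases against hospital controls.** If a share h of the 64 controls comes from hospital records, the standard error is 10 × √(1/64 + 1/(64h)).

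| h | Hospital controls | SE (mm Hg) | 95% CI half-width (mm Hg) | Power for 5 mm Hg |
|---|---|---|---|---|
| 100% | 64 | 1.77 | 3.46 | 80% |
| 75% | 48 | 1.91 | 3.74 | 74% |
| 50% | 32 | 2.17 | 4.24 | 63% |
| 25% | 16 | 2.80 | 5.48 | 42% |

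**The case against.** **The covariate list is open.** A reader might infer that diabetes has been excluded from the model. The text does not support that: the list is introduced as examples, and an analysis plan that is not shown may complete it. What the article supports is that diabetes is not named while the other two matching factors are. That mismatch is on the page.

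**Diabetes is already balanced by design.** This largely stands. Matching limits the imbalance, and the residual bias is small even under the assumptions. Naming diabetes is a cheap consistency repair.

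**Control source is a recruitment route, not a matching or stratification factor.** This also stands. It varies only among controls, so it cannot be balanced between groups as an ordinary covariate can. An indicator for advertised controls, beside the COVID-19 term, is still estimable: it codes three groups with two terms.

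**The bias may be small, or not in favour of an effect.** A reader might infer that the design inflates the COVID-19 effect by comparing recently hospitalised patients with healthy volunteers. The documents do not establish this. New patients are invited at least 12 weeks after discharge and the outcome is at 12 months, so recent is the wrong word. Nothing requires advertised controls to be healthy volunteers. All participants have no history of hypertension and take no pressure-lowering drugs, and BMI is adjusted for, which may narrow any gap. The 48 pilot participants are to be invited, and any pilot controls who join were admitted. These points make size and direction uncertain; they do not remove the possibility.

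**The secondary models may deal with it.** They do not repair the primary estimate. One leaves its covariates unnamed. The other adjusts for a baseline pressure measured after COVID-19 in the cases, so it can also absorb part of the effect under study.

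**Conclusion.** The point holds in a limited form. Diabetes is a matching factor that the primary model does not name, which is a minor inconsistency worth about 0.25 to 0.8 mm Hg under the assumed imbalance and effect. The more important part is that all cases were admitted, advertised controls need not have been, their share is not stated, and no comparison restricted to hospital controls is given. The primary coefficient can therefore carry a difference due to admission or control selection: 0.6 to 2.0 mm Hg under the assumed share and gap, or 12% to 40% of the target difference.

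Every magnitude here rests on assumptions, and the direction is not known from the article. The conclusion is that the primary contrast cannot by itself separate the two explanations, not that it is shown to be biased upwards.

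**What to change.** 1. In Statistical analysis, name diabetes status as a covariate of the primary regression, so that all three matching factors are in the model.
2. Record for each control whether recruitment was from admission records or by advertisement.
3. Pre-specify one sensitivity analysis: the primary model plus an indicator equal to 1 for advertised controls and 0 for cases and hospital controls. The COVID-19 coefficient then compares cases with hospital controls. Restricting the analysis to cases and hospital controls is an acceptable alternative.
4. Report that estimate with its 95% confidence interval beside the primary one. If the effect is materially smaller against hospital controls, limit the causal wording of the conclusion.

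**Cost.** The change is to analysis wording, since both variables are known at recruitment. Diabetes uses about one degree of freedom. The primary sample size is unchanged. The sensitivity estimate loses precision as the share of hospital controls falls. The two estimates will also differ somewhat by chance, so the sensitivity result should be read by its size and interval, not as a second significance test.
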